### Sample size calculation

As AAV is uncommon, the required sample size was optimised using a phase II selection theory approach (also known as ‘pick the winner’) as proposed by Simon et al. [34]. The treatment which is ranked as having the lower proportion of patients with uncontrolled AAV (BVAS > 3) (or controlled but with > 7.5 mg prednisolone or other corticosteroid daily) in the final 12 weeks of the study will be selected as the ‘winning treatment’.

A sample size of 72 patients (36 in each arm) will be required to provide 90% probability of correctly ranking hydroxychloroquine as superior to placebo, assuming 50% of patients in the placebo group have uncontrolled AAV (or controlled but with > 7.5 mg prednisolone or other corticosteroid daily) in the final 12 weeks of the study and assuming that the true reduction in this rate due to hydroxychloroquine is 15%. This trial is not designed to demonstrate a statistically significant difference between the two arms, so the type I error rate does not apply.

Seventy-six participants will be recruited to allow for a 5% drop-out rate. This drop-out rate is based on similar trials which had a < 5% drop-out rate [21, 32, 33].

### Data management and monitoring

A web-based electronic data capture system has been designed using the InferMed Macro 4 system hosted by the King’s College London Clinical Trials Unit (KCTU). No identifiable data beyond participant initials, age at consent and year of birth will be entered on the electronic case report form (eCRF), and no data will be collected unless a participant has signed a consent form. Participants will be assigned a unique trial number upon entry to the trial, ensuring that all trial data is pseudonymised.

Source data worksheets will be used to collect data, and these will be transcribed to the eCRF. The FACIT, SF-36, EQ5D, HAQ and AAV Pro questionnaires will be used to collect quality of life data. Lab sample results will be transcribed to the eCRF from medical records.

Trial monitoring will be provided by the King’s Health Partners Clinical Trials Office (KHP-CTO). The clinical research associate (CRA) will perform source data verification and raise queries with the trial site staff. Missing data and discrepancies will be reviewed and queried by the trial’s data manager to ensure data quality prior to each extract.

#### Quality assurance

All clinicians scoring BVAS and VDI will be trained and certified prior to recruitment of participants. An adjudication committee blinded to treatment group will scrutinise all the BVAS and VDI scores and major and minor relapses. The adjudication committee will provide advice and further training where appropriate to ensure consistency across sites. The committee is chaired by [name], one of the sites’ principal investigators. He is the leading expert on BVAS and VDI.

#### Safety

All serious adverse events (SAEs), serious adverse reactions (SARs) and suspected unexpected serious adverse reactions (SUSARs) related to trial procedures will be reported immediately (and no later than 24 h) by the investigator to the KHP-CTO and chief investigator (CI) for review in accordance with their Pharmacovigilance Policy. Adverse events related to disease activity will be recorded as part of BVAS and so will not be reported separately. All data regarding the occurrence of adverse events will be made available to the DMC for review.

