#### Trial oversight

The trial has a DMC, TSC and TMG.

The DMC meet every 6 months. The committee has access to unblinded accumulating comparative data and is comprised of independent members. The DMC is responsible for monitoring the accumulating data and making recommendations to the TSC on whether the trial should continue as planned. Only the DMC and a partially unblinded statistician has access to the unblinded accumulating data.

The TSC meet following each DMC meeting and is responsible for oversight of the trial in order to safeguard the interests of trial participants. The TSC provides advice to the CI, KHP-CTO, the funder and sponsor on all aspects of the trial through its independent chair. The BVAS adjudication committee feed into the TSC as needed.

The TMG is responsible for the day-to-day running and management of the trial and meet on a monthly basis. Sites will be invited to attend the TMG to inform them of trial amendments and provide a forum for feedback and recruitment information.

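### The only 24-hour serious-event rule carries a qualifier about trial procedures that is either too narrow for a drug trial or has no function

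*Protocol article*

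**What the plan says.** The Safety section of the protocol article contains a single expedited reporting rule. It opens: "All serious adverse events (SAEs), serious adverse reactions (SARs) and suspected unexpected serious adverse reactions (SUSARs) related to trial procedures will be reported immediately". The same sentence puts the outer limit at 24 hours and names the route: "by the investigator to the KHP-CTO and chief investigator (CI) for review in accordance with their Pharmacovigilance Policy".

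Two further statements follow in that section. The first is an exemption: "Adverse events related to disease activity will be recorded as part of BVAS and so will not be reported separately". The second concerns oversight: "All data regarding the occurrence of adverse events will be made available to the DMC for review".

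Elsewhere, Trial oversight says "The DMC meet every 6 months" and "The TMG is responsible for the day-to-day running and management of the trial and meet on a monthly basis". Data management and monitoring says "The clinical research associate (CRA) will perform source data verification and raise queries with the trial site staff". Table 1 has a row for adverse event collection at scheduled contacts from baseline onward. Trial status says that the trial runs to protocol version 6.0, dated 10 May 2022.

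**The concern.** HAVEN compares a drug with placebo, so its expedited rule should turn on seriousness and should certainly cover reactions to the drug. The rule instead ends with a qualifier about trial procedures, which in this trial are things such as visits, blood sampling and ECGs. A site working from this sentence could not tell whether it must send in, within 24 hours, a serious event that has nothing to do with a procedure.

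What is at stake is prompt central review of causality and expectedness for individual serious events. The article itself shows why that review has value here. The Background describes a population with a threefold cardiovascular risk. The Discussion cites a study reporting raised cardiovascular risk with hydroxychloroquine after 30 days of continuous use, and says that the protocol was amended to exclude long-term macrolide users and to restore a week-16 ECG. For a serious cardiac event, the underlying disease and the drug are both candidate causes. Whether such an event is reported quickly should not depend on how one phrase is parsed.

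**Working it through.** No arithmetic applies. The check sets out the two grammatical readings of the rule, applies each to the kinds of serious event that can occur, and then looks for any other deadline in the article. It assumes the usual nesting of the terms, which the article does not define: SARs are SAEs with a suspected causal link to the study drug, and SUSARs are the unexpected ones among them.

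**Step 1: the two readings.** One opening quantifier introduces a list of three terms, one qualifier closes it and one verb follows.
- Reading A: the qualifier governs all three terms.
- Reading B: the qualifier governs only the last term, SUSARs.

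**Step 2: what each reading covers.**

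| Serious event | Reading A | Reading B |
|---|---|---|
| Caused by a trial procedure | 24 h | 24 h |
| Unrelated to drug or procedure | no deadline stated | 24 h |
| Expected reaction to the drug, not procedure-related | no deadline stated | 24 h |
| Unexpected reaction to the drug, not procedure-related | no deadline stated | 24 h, because it is also an SAE |
| Disease activity recorded in BVAS | exempt | exempt |

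Under A, three of the five rows have no stated deadline, and two of those three are reactions to the study drug. That cannot be the intended scope of a drug trial's rule. Under B, the qualifier changes no row and could be deleted without effect.

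**Step 3: is there another deadline?**
- Table 1 says when sites ask about adverse events, not when the trials office or chief investigator must be told.
- Source data verification (Data management and monitoring) carries no reporting deadline.
- The monthly TMG meeting (Trial oversight) carries none.
- The DMC receives all adverse event data (Safety) and meets every 6 months (Trial oversight). That is periodic review, not expedited reporting.

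So the 24-hour limit is the only reporting deadline in the article, and it sits in the sentence whose scope is unclear.

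**The case against.** The strongest case on the other side has three parts.

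First, the sentence opens by naming all SAEs and lists them separately from SARs and SUSARs. That suggests the authors meant every SAE to be covered and that the trailing phrase is loose drafting. This stands as a view of what was intended, and it is why the wording is called ambiguous. It does not rescue the sentence, which still contains a phrase that does either harm or nothing.

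Second, the sentence defers to a Pharmacovigilance Policy, and the full protocol is version 6.0. Neither is shown, and an article may properly leave reporting detail to them. This stands too, and it limits the point to the article's text. It does not remove the point, because the article has not left the scope out. It has stated a scope, and stated it badly.

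Third, events outside the rule are not lost, since the DMC sees all adverse event data. That is correct. What is missing is a clear deadline, not a record.

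A reader might go further and infer that the rule clearly excludes unrelated SAEs while still covering drug reactions. Neither reading gives that result. If the qualifier reaches SAEs across the list, it reaches SARs and SUSARs as well. If being named in the list protects those two, it protects SAEs equally. A reader might also infer that the blinded site must judge relatedness before the deadline applies. The article says that the investigator reports and that research staff are blinded, but it does not say who assesses relatedness.

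**Conclusion.** The point holds as a minor fault of wording. The scope of the only 24-hour rule is too narrow on one reading and carries an idle phrase on the other, and no other part of the article supplies a deadline.

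Its size cannot be put in numbers. The article does not allow the number of affected events, or the time any of them would wait, to be derived. The spacing of visits and of DMC meetings does not measure either. No endpoint, sample size or analysis is affected.

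The documents do not support a conclusion that serious events are in fact going unreported in HAVEN. That would require the Pharmacovigilance Policy and protocol version 6.0, which may already require all SAEs within 24 hours. Nor would the correction reveal a difference between arms any sooner, since "Only the DMC and a partially unblinded statistician has access to the unblinded accumulating data". The gain is clear, prompt review of individual events.

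**What to change.** In the Safety section, delete the four words between the SUSAR abbreviation and the verb. State that the investigator reports all SAEs within 24 hours of the existing trigger, whatever their judged causality, except the disease-activity events recorded in BVAS, which stay exempt as the section already provides.

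Before amending anything else, check protocol version 6.0 and the Pharmacovigilance Policy. If they already say this, only the article sentence needs correcting. If they carry the same qualifier, amend them in the same way and tell the sites.

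The cost is one sentence and, at most, a few more expedited reports to the trials office and chief investigator.

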#### Trial oversight

The trial has a DMC, TSC and TMG.

The DMC meet every 6 months. The committee has access to unblinded accumulating comparative data and is comprised of independent members. The DMC is responsible for monitoring the accumulating data and making recommendations to the TSC on whether the trial should continue as planned. Only the DMC and a partially unblinded statistician has access to the unblinded accumulating data.

The TSC meet following each DMC meeting and is responsible for oversight of the trial in order to safeguard the interests of trial participants. The TSC provides advice to the CI, KHP-CTO, the funder and sponsor on all aspects of the trial through its independent chair. The BVAS adjudication committee feed into the TSC as needed.

The TMG is responsible for the day-to-day running and management of the trial and meet on a monthly basis. Sites will be invited to attend the TMG to inform them of trial amendments and provide a forum for feedback and recruitment information.

### Statistical analysis

Due to the use of a selection theory (pick the winner) approach, the main analysis will not include inferential analysis. Instead, the main analysis will involve presenting the descriptive statistics for each treatment arm to demonstrate which treatment is selected (i.e. which treatment group has a lower proportion of participants meeting the primary endpoint criteria). Due to this trial design, no interim analyses have been planned.

The descriptive statistics follow those specified in the outcome measures. The primary outcome and secondary/exploratory outcomes specifying a proportion will be described as the number and proportion of participants meeting that outcome. Secondary/exploratory outcomes specifying median will be described as median and range. Secondary/exploratory outcomes specifying mean will be described as mean and standard deviation.

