
At trial entry, eligible participants will have uncontrolled disease, which is defined as BVAS > 3. Over the course of the study, a participant may have a limited or severe flare, persistent disease, or they may enter remission. A limited flare is defined as a new or worsening minor item on the BVAS with no new major items, whereas a severe flare includes a new or worsening major item. Persistent disease indicates the presence of one or more ongoing items on the BVAS with no new or worsening items, while remission is defined as a BVAS of 0 on two consecutive visits planned to be at least 4 weeks apart.

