### Outcome measures

The primary outcome is the proportion of patients at any point during the final 12 weeks of the study (± 7 days) with uncontrolled AAV disease activity (defined as BVAS > 3) OR with controlled AAV disease activity (BVAS ≤ 3) but prednisolone dose for AAV > 7.5 mg daily OR with controlled AAV disease activity (BVAS ≤ 3) but any corticosteroid use > 7.5mg daily for any reason*.

The following secondary outcomes will be examined:Median cumulative number of visits where BVAS = 0 experienced by each patient (excluding screening, baseline and week 56)Proportion of patients with deemed treatment failure at week 52Mean cumulative dosage of prednisolone*Total number of adverse events per treatment arm*Median cumulative number of infections experienced by each patientMedian number of vasculitis flares (major and minor) experienced by each patient (excluding those as screening, baseline and week 56)Median time from randomisation to remission (BVAS = 0 on two consecutive visits at least 4 weeks apart)Median time to the first severe flare with starting time points of randomisation and remission (if achieved)Median time to the first limited flare with starting time points of randomisation and remission (if achieved)Proportion of patients categorised as having a severe flare at each time point (excluding screening, baseline and week 56)Proportion of patients categorised as having a limited flare at each time point (excluding screening, baseline and week 56)Median absolute Vasculitis Damage Index (VDI) [24] at each time point and the median relative change in VDI from baseline to each time point

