#### Subgroup/exploratory analyses

The reporting of descriptive statistics for the primary endpoint and ranking of the two treatment arms will be repeated for the following subgroups:Those deemed compliant with treatment (consumption of > 80% of provided tablets)Those deemed non-compliant with treatment (consumption of ≤ 80% of provided tablets)

These analyses will only be repeated if enough participants meet these criteria for each treatment arm (≥ 5 participants per group).

Additionally, exploratory inferential analyses have been planned. This will involve tests of two proportions for those outcomes specifying a proportion. For the other outcomes, unpaired *t*-tests and Mann Whitney *U* tests will be used dependent on the resultant outcome distribution. For all tests, a one-sided significance level of 10% will be used to determine results of potential interest.

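### Times to remission and to flare are right-censored, but the plan summarises and tests them as complete data, so the results can hide, reverse or invent an effect

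*Protocol article*

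**What the plan says.** Outcome measures lists three times among the secondary outcomes. One is "Median time from randomisation to remission (BVAS = 0 on two consecutive visits at least 4 weeks apart". The second is "Median time to the first severe flare with starting time points of randomisation and remission (if achieved", and the limited-flare outcome is worded in the same way. Each flare outcome therefore has two clocks, and the second exists only for participants who remit.

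Statistical analysis sets one summary for all such outcomes: "Secondary/exploratory outcomes specifying median will be described as median and range". Subgroup/exploratory analyses gives proportions a two-proportion test, then states: "For the other outcomes, unpaired *t*-tests and Mann Whitney *U* tests will be used dependent on the resultant outcome distribution". The threshold is also fixed: "For all tests, a one-sided significance level of 10% will be used to determine results of potential interest".

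The article expects participants without the event. The paragraph that closes the eligibility criteria says that "a participant may have a limited or severe flare, persistent disease, or they may enter remission". Neither section mentions censoring, Kaplan-Meier, log-rank or Cox, or makes an exception for the time outcomes.

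**The concern.** A participant who has not remitted or flared by week 52, or who withdraws first, contributes only the fact that the time exceeds the last visit. A median with range, a t-test and a Mann-Whitney test all need a complete value for each person. To apply them, the analyst must either drop participants without the event or enter the censoring time as if it were an event time.

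The article calls itself a protocol and statistical analysis plan, and its two rules cover these outcomes by their terms. This is therefore a stated method that does not suit the data, not a detail left to another document.

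The stake is the reading of secondary results. The abstract names flares and time to remission among the secondary outcomes, the exploratory tests are meant to pick out results of interest, and the Discussion foresees a further study if hydroxychloroquine ranks better.

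**Working it through.** **Inputs.** From the article: 36 per arm, 52 weeks on treatment, BVAS visits at weeks 4, 16, 28, 40, 44, 48 and 52, planned drop-out 5%, one-sided 10%. The article gives no remission or flare rates and no figure for the time outcomes, so there is none to reproduce. All event rates below are assumptions, with exponential times unless stated.

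**1. What the median describes.** If a proportion p has the event by week 52, the weekly hazard is λ = −ln(1−p)/52 and the true median is ln 2/λ. The median among those with the event is −ln(1−p/2)/λ.

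| Assumed p | λ per week | True median (weeks) | Median among events only (weeks) |
|---|---|---|---|
| 30% | 0.3567/52 = 0.00686 | 0.6931/0.00686 = 101 | 23.7 |
| 15% | 0.1625/52 = 0.00313 | 222 | 24.9 |
| 60% | 0.9163/52 = 0.01762 | 39 | 20.2 |
| 40% | 0.5108/52 = 0.00982 | 71 | 22.7 |

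The severe-flare contrast of 30% v 15% has hazard ratio 0.1625/0.3567 = 0.46. The events-only medians differ by about one week, and neither true median is reached within the trial. For 60% v 40% (hazard ratio 0.56) the difference is 2.5 weeks.

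**2. Chance of flagging a real effect, clock from randomisation.** Simulated trials, 36 per arm, one-sided 10%, drop-out 0-5%; Monte Carlo standard error about √(0.6×0.4/2,500) = 1 point.

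| Flare rates | Mann-Whitney, events only | Mann-Whitney, everyone kept | Log-rank |
|---|---|---|---|
| 30% v 15% | about 11% | 53-61% | 59-61% |
| 60% v 40% | 16-18% | 65-67% | 67-68% |

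For remission 30% v 45%, with events recorded at the scheduled visits and 5% drop-out, log-rank flags 52%. Using remitters only, either test flags 15%. Keeping everyone, Mann-Whitney flags 47% and the t-test 42%. At 20% drop-out, Mann-Whitney with everyone kept falls to 38%, against 49% for log-rank.

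**3. The sign can reverse.** Suppose remission is 30% v 45% and the drug raises the remission hazard 2.5-fold, but only after week 28. The median among remitters is then 38 weeks on the drug and 30 on placebo. Mann-Whitney in remitters flags the drug as worse in 32% of trials and as better in 1.5%. Log-rank flags the benefit in 49%.

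**4. Clock from remission.** Follow-up is 52 minus the week of remission, so earlier remission gives longer follow-up. Simulate no effect on flare hazard but earlier remission on the drug. With remission spread over weeks 4-28 v 16-44, all participants remitting, and a 52-week flare rate of 30% or 50%, a false benefit is flagged as follows:

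- Mann-Whitney, events only: 28-39%.
- Mann-Whitney, censored time used as the value: 98-100%.
- Log-rank: 10%.

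A second set of runs with other assumed settings gave 10-29%, 75-98% and about 10% respectively. The nominal level is 10%. Log-rank holds it here because these simulations make flare hazard independent of who remits and when. The documents do not guarantee that.

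**5. What is untouched.** The sample size rests on the primary proportion. With 36 per arm and 50% v 35%, the exact probability of correct ranking, ties split evenly, is 90.2%, so the stated 90% reproduces. Allowing for drop-out, 72/0.95 = 75.8, that is 76.

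**The case against.** The strongest reply is that the article nowhere says participants without the event are dropped. If all are kept and nearly all censoring falls at week 52, as the expected withdrawal below 5% implies, those participants tie at the top rank. Mann-Whitney from randomisation then holds its nominal level (9-10% with no true effect) and loses only a few points to log-rank. This stands for the randomisation clock. It does not rescue the median and range, the t-test, or the clock from remission, where follow-up can differ by arm.

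A reader might infer that the plan hides a real flare effect, with about an 11% chance of seeing it. The documents do not support that. The figure belongs to one of two possible handling rules, and Outcome measures separately lists flare counts and the proportions with severe and limited flare, to which two-proportion tests apply. Those proportions are by time point, so they mitigate the problem but do not replace a time-to-event analysis.

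A reader might also infer that the arm with more remissions contributes more fragile ones. Nothing in the article shows this. The firm point is that the subset is formed after randomisation and follow-up within it can be unequal.

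Finally, "the main analysis will not include inferential analysis": treatment is selected on the primary proportion alone, and the tests criticised here are exploratory. That stands and limits the severity.

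**Conclusion.** The point holds as a fault of method in three secondary outcomes and should be fixed. The plan treats right-censored times as complete data, and the error can run in either direction.

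For times from randomisation the damage runs from slight (everyone kept, little drop-out) to severe (events only), and the article does not say which would apply. Where fewer than half of an arm has the event, the true median is not reached, and a median taken from observed event times describes only those participants.

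The clock from remission is the more serious part, since a false benefit can be flagged well above 10%. Its size depends on assumed remission times: some events-only settings stayed near 10%, while using censored times as values gave 75-100%.

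None of this alters the primary ranking or the sample size, so it is not a must-fix.

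**What to change.** For these three outcomes, replace the general rule with the following:

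- Kaplan-Meier estimates by arm: the median where it is reached, otherwise the event-free proportion at week 52 with a confidence interval.
- A log-rank test or Cox model for the exploratory comparison from randomisation.
- A stated censoring rule: the last BVAS visit up to week 52, for participants without the event and for those who withdraw.
- Flare after remission shown by Kaplan-Meier, descriptively, with no test between arms.

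The cost is analysis-plan wording and code. No new data, visits or participants are needed, and the change should be made before unblinding.
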